#### Evaluation plan

The evaluation plan is intended to compare the effectiveness of three promising strategies for implementation of the tobacco use treatment guidelines, to examine multi-level, theory-driven mechanisms (organizational priority, provider beliefs) hypothesized to explain the effectiveness of the three strategies for implementation, and finally to identify multi-level barriers and facilitators that that may influence the implementation of evidence-based tobacco use treatment practices in dental care settings. Mixed methods (*i.e.*, site observational, interview and survey) data will be collected from patients, providers, dental directors, dental charts and Quitline referral data. For clarity, the assessment plan is organized according to following evaluation domains: primary outcomes, secondary outcomes, process outcomes, organizational setting moderators, implementation fidelity, and provider demographics.

### Outcome evaluation (aim one)

#### Primary outcome

To assess the primary outcome of provider adherence to tobacco use treatment guidelines, we will conduct and compare pre- and post-intervention patient exit interviews conducted with eligible smokers at each of the 18 clinic sites. Prior to beginning of the implementation intervention, we will conduct 100 patient exit interviews (n = 1,800 pre-intervention) at each clinic site. Then, after each site has completed the planned intervention, another independent sample of 100 smokers will complete patient exit interviews (n = 1,800 post-intervention). Patient interviews conducted at the point of service are considered to be the optimal non-observational method for measuring provider delivery of outpatient treatment [58,59]. A modified patient exit interview (PEI) [60] will be used as a brief patient-reported measurement tool for the assessment of provider delivery of tobacco use screening and treatment. A PEI index (summary) score is determined by adding the number of tobacco treatment behaviors each patient reports that the provider implemented during the most recent visit. PEI index will scores range from 0 to 8. The questions assess the full spectrum of PHS guideline recommended care (*i.e.*, 5As). For example, patients are asked if their provider advised them to quit, offered cessation counseling and/or discussed cessation medications. The PEI has well-established validity as evidenced by strong correlation with more costly audio-taped assessment of physician-patient interactions (r = 0.67, p < 0.001) and has been commonly used to accurately measure providers’ delivery of tobacco cessation assistance efforts during office practice, and to monitor providers’ adherence to tobacco cessation treatment guidelines in clinical trials. Prior to and approximately nine months following each site’s enrollment, consecutive patients will be approached during their clinic visits by trained research study assistants (RSA), to determine current smoking status and to obtain consent for the PEI. Patient eligibility will include those: age 18 or over; English- or Spanish-speaking; current smokers defined as those who report smoking within the past seven days; New York State residents; and who have an appointment with a dentist or hygienist for routine non-emergent care. Immediately after their dental visit, patients will complete the PEI to assess provider adherence to the PHS Guideline (5As). We expect that most surveys will be administered using a computer tablet with a password protected, web-based data entry portal (REDCap) [61]; however, paper surveys will be available, as needed.

#### Cost analysis

Following recommendations for cost assessment methodology described by Ritzwoller *et al.*, [62] research costs (*e.g.*, labor and other inputs associated with grant administration, IRB approval, manuscript preparation), and direct clinical intervention costs (*e.g.*, dental provider time associated with counseling patients, staff training, IT costs, reimbursement costs) will be estimated. Templates have been developed to capture data prospectively to improve accuracy and precision of cost assessment. The NYS Quitline has estimates of their counseling cost per quit. The costs of the medications taken by the patients as part of their cessation attempt (reported at the three-month telephone survey) will be estimated. In addition, as part of the follow-up assessment, patients will complete the EQ5D, which is a commonly used patient self-report measure of health status. Applicable to a wide range of health conditions, this measure provides a single index value for health status that can be used in the clinical and economic evaluation of healthcare^.^[63].

#### Secondary outcomes

To assess patient utilization of cessation services and smoking abstinence, follow-up telephone interviews, three months post-clinic visit, will be conducted with smokers who complete the post intervention PEIs. A standardized interview will be used to collect patient-reported cessation outcomes including seven-day abstinence and 24-hour quit attempt and use of cessation treatment during the past three months.

### Implementation process evaluation (aim two)

The process evaluation encompasses three areas: TPB processes; Solberg’s construct of Organizational change priority; and acceptability of and satisfaction with the implementation strategies. The multiple data sources (Table 3) include: surveys with participating dentists and dental directors; de-identified data from quarterly chart audits conducted by clinic administrative staff of clinical documentation of tobacco treatment delivery; site observations; de-identified monthly reports from the NYS Quitline summarizing the number of referrals received; and semi-structured interviews with dental clinic directors.

**Table 3 T3:** Evaluation data sources

	**Data source**	**Tool**	**Source**	**Administration**	**Variables**
**Primary outcome**	Patients	Patient Exit Interview (PEI)	[60]	Baseline, nine months following site enrollment	Provider adherence to PHS Guidelines for Treating Tobacco Dependence
**Secondary outcomes**	Patients	Patient Outcomes Survey		Three months after post- PEI	Use of tobacco treatment services, 24-hour quit attempt, Smoking abstinence (7 day point prevalence)
	Research staff and patients	Cost collection template, EQ5D	[62,63]	Ongoing	Costs per quit, QALY, Research and clinical intervention costs
**Process outcomes**	Dental Providers	Provider Attitudes Survey	[42,48,50,64-66]	Baseline, 4.5, and nine months following site enrollment	Provider attitudes, norms, perceived behavioral control, intentions, perceived organizational priority of tobacco use treatment
		Provider Practice Behaviors	[1]	Baseline, 4.5 and nine months following site enrollment	Provider adherence to PHS Guidelines for Treating Tobacco Dependence
		Semi structured Interviews		Nine months following site enrollment	Provider attitudes and practice behaviors
**Organizational setting moderators**	Dental Directors	Organizational Structure Survey	[67-70]	Baseline	Dental staff FTE, patient volume, pay or mix, staff/clinic/patient characteristics
		Change Process Capability Questionnaire	[71]	Baseline	Organizational readiness, change capacity
		Semi structured Interviews		Nine months following enrollment	Organizational implementation and change processes
**Implementation fidelity**	Site observations	Site assessment tool		4.5 and nine months following site enrollment	Pre and post intervention chart and referral systems, workflow
	Dental Chart	Chart audit form		Baseline and Quarterly	Documentation of adherence to tobacco use treatment guidelines
	NYS Quitline	Quitline referral reports		Baseline and Quarterly	Confirmation of changes in Quitline referral patterns
**Provider demographics**	Dental Providers	Provider Demographics		Baseline	Role, degree, years of practice, smoking status, gender

#### Dental director and provider surveys

Measures for four TPB variables (attitudes, subjective norms, perceived behavioral control, and intentions) are based on modifications of selected subscales from established survey tools developed by Park [66], Amemori [64], Francis [50] and Grimshaw *et al.*[48] to assess knowledge and attitudes regarding treatment of tobacco dependence, clinic norms, and perceived behavioral control, and intentions. We will use a modified version of the Perceived Organizational Priority Survey [65] to assess the perceived priority of tobacco use treatment at the dental clinic. We also adapted a tool by Weiner *et al.* to measure additional organizational factors that may influence provider behavior [42]. Semi-structured interviews will be done after completion of the intervention period with the dental director at each of the participating dental clinics. The interviews will focus on site-specific barriers and facilitators of strategy implementation, the process of integrating and customizing the implementation strategy into the clinic site workflow as well as acceptability and satisfaction.

### Baseline organizational characteristics (aim three)

#### Organizational change capacity

The Change Process Capability Questionnaire (CPCQ) will be used to assess baseline measures of organizational capacity to change [71]. The survey measures several domains of change capacity: history of change, plans for continuous organizational refinement, ability to initiate and sustain change, and strategies for process improvement.

#### Organizational structure

At baseline, data on organizational variables shown to influence implementation of provider practice guidelines including number of full-time equivalent staff, insurance payer mix, hospital-based or freestanding clinic, academic affiliation, clinic volume, and staff characteristics will be collected [67-70,72]. Dental directors will complete surveys in order to identify pre-intervention clinical systems and policies (*e.g.*, electronic or paper chart system).

#### Implementation fidelity

We will use several approaches to measure fidelity of the three implementation strategies [73].

#### Current best practices

At baseline, site observations will be conducted to assess clinical processes and workflow (*e.g.*, patient registration, how referrals are handled, who currently screens patients for tobacco use) and these site observations will be repeated at 4.5 and 9 months following site enrollment. During these site visits, use of the dental chart system and Refer-to-Quit forms will be determined. NYS Quitline data will be used as an additional source of information to confirm increases in referral rates in the post intervention period. The NYS Quitline provides monthly reports that include the number of referral forms received by a specific site and provider. In addition, the percentage of clinical staff members who attend the CBP initial and booster training will be recorded.

#### Chart audits and PF

The dental directors will be queried at three, six, and nine months to confirm date of distribution of the quarterly PF reports.

#### Pay for performance

The dental directors assigned to P4P will be also asked at 3, 6, and 9 months to confirm receipt of the quarterly financial incentive earmarked to performance of tobacco treatment interventions.

### Statistical considerations and analytic plan

#### General approach

Eighteen dental clinic sites will be recruited and randomly assigned to one of three implementation strategies in a cluster-randomized design. The general statistical paradigm for assessing outcomes will be based on a Multi-Level Model (MLM) approach [74] (also known as ‘hierarchical linear model’) [8,32,75,76]. MLM adjusts for the clustering effects across multiple levels (patients, providers, dental clinics) of hierarchical data structure. Before the implementation strategies are rolled out, 100 patients per site will be assessed through standardized PEIs to establish the baseline level of dental provider assistance in tobacco cessation. Then each site will be randomly assigned and will receive their intervention condition for nine months. Following the intervention period, 100 new patients from each site will be recruited for assessment of post-intervention changes in provider adherence to the guidelines.

#### MLM approach to address the primary aim

A two-level MLM will test of the effectiveness of the implementation strategies. The primary outcome is the summary score of the PEI assessment of provider assistance (score range 0 – 8). At level one, we will enter each patient’s PEI score of dental provider assistance as a function of intervention and time (pre and post intervention), thereby allowing each site to serve as its own pre-implementation control, an added benefit to minimize an order effect, (*e.g.*, sites that enter the active implementation phase later may derive greater benefits due in part to improved efficiency in logistics coordination) [75-77]. Additional covariates may also be included (*e.g.*, patients’ age, gender, and education).

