### Performance feedback (PF)

In recent randomized trials conducted in primary medical care settings, clinical audit and feedback with regard to tobacco treatment performance have been associated with a twofold increase in providers’ adherence to cessation assistance and referral to cessation quitlines [16-18,21,23-25]. The potential value of these strategies has not yet been fully examined in dental practice. A single arm, pilot study tested the feasibility and promise of implementing CBP plus provider feedback in six public dental clinics in New York City [26]. The main outcome measure—provider adherence to tobacco use treatment guidelines—was assessed by auditing a random selection of dental chart documentation pre and post-adoption of this implementation strategy. Following implementation of CBP and PF, providers were significantly more likely to offer advice (28% pre, 49% post), assess readiness to quit (18% pre, 30% post), and offer assistance (7% pre, 16% post) [26,27].

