### Pay for performance (P4P)

P4P or providing financial incentives for meeting predetermined performance goals has attracted much interest as a strategy to improve quality of care [28,29]. The European Workshop on Tobacco Use Prevention and Cessation for Oral Health Professionals emphasized the importance of appropriate compensation (incentives) of tobacco use treatment [30]. Several studies have demonstrated a positive association between P4P and adherence to recommended tobacco use treatment [31-33], including increased referrals to statewide tobacco quitline services [31].

Using a three-arm cluster randomized controlled trial design, the overall objective of this protocol is to compare the effectiveness of three promising implementation strategies designed to address organizational and provider level challenges for effective treatment of tobacco dependence. Guided by a multi-level, conceptual framework that emphasizes both provider beliefs and organizational characteristics, the trial will be conducted in 18 public dental care clinics in New York City and information about implementation outcomes and processes will be captured with multiple data sources (patient exit interviews, provider surveys, site observations, chart audits, and semi-structured provider interviews) in order to examine factors that influence the implementation process.

The specific aims of this comparative effectiveness research trial are to:

1. Compare the effectiveness and cost of three promising strategies for implementation of the PHS tobacco use treatment guidelines on dental provider delivery of cessation assistance:

a) Staff training and CBP;

b) CBP + provider PF; and

c) CBP + PF + provider reimbursement for delivery of tobacco cessation treatment (pay-for- performance; P4P)

2. Use a mixed-methods approach to examine potential theory-driven mechanisms at the organizational and provider level hypothesized to explain the comparative effectiveness of three strategies for implementation;

3. Identify baseline organizational factors that influence the implementation of evidence-based tobacco use treatment practices in dental clinics.

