The central hypothesis is that the value of these promising implementation strategies is additive and that instituting all three strategies (CBP, PF, and P4P) will be superior to CBP alone and CBP + PF in increasing delivery of cessation assistance to smokers. The ultimate goal is to provide critical new knowledge to facilitate the widespread implementation, dissemination and sustained utilization of evidence-based tobacco use treatment strategies in dental practices.

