## Methods

### Overview of study design

As shown in Figure 1, a three-arm cluster randomized controlled trial will examine the tobacco treatment guideline implementation process and compare the cost and effectiveness of three implementation strategies: Staff training and CBP in implementing PHS Guidelines; CBP + PF; and CBP + PF + pay-for-performance (provider reimbursement for tobacco cessation treatment delivery). Guided by Organizational Change Theory and the Theory of Planned Behavior (TPB) [34-37], multi-level factors that facilitate or impede the implementation process will be identified. The primary outcome is improvement in dental provider delivery of tobacco cessation treatment. Secondary outcomes are cost per quit, use of tobacco cessation treatments, quit attempts and smoking abstinence. A mixed methods (survey, semi-structured interview, chart audit, site observation and NYS Quitline referral report) approach will be used to examine implementation processes (aim two).

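### The 0-8 exit-interview score counts behaviours across all 5As but is labelled and tested as provider assistance, and the assistance rate that was powered is in no outcome list

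*Protocol article*

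**What the plan says.** All references are to the protocol article.

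- **Target.** Aim one compares strategies for implementing the "tobacco use treatment guidelines on dental provider delivery of cessation assistance". The central hypothesis is that the three-component arm "will be superior to CBP alone and CBP + PF in increasing delivery of cessation assistance to smokers".
- **How the score is built.** The Primary outcome section forms the patient exit interview (PEI) index by "adding the number of tobacco treatment behaviors each patient reports that the provider implemented during the most recent visit", with a range of 0 to 8. On content it says: "The questions assess the full spectrum of PHS guideline recommended care". Its three example items are advice to quit, an offer of counselling and discussion of medication.
- **How the score is labelled.** Under MLM approach to address the primary aim: "The primary outcome is the summary score of the PEI assessment of provider assistance". The section on statistical power then tests PEI scores against a null that assistance behaviours are equal across conditions.
- **What else is listed.** The Overview of study design states: "Secondary outcomes are cost per quit, use of tobacco cessation treatments, quit attempts and smoking abstinence". The abstract gives the same list. Table 3 names patient use of services, quit attempts, abstinence and costs as secondary. It places provider self-report under process outcomes, and chart audit and Quitline reports under implementation fidelity.
- **What is powered.** The power section names two key components: the omnibus PEI effect and differences in provider assistance rates. For the rates it assumes 10%, 20% and 30% by arm and a logistic GEE, with a two-sided type I error of 0.01 and an ICC of 0.22.

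**The concern.** The Background treats the 5As as separate steps, of which assisting is one. It also places the gap in dental care at that step: screening and advice are increasing, while routine assistance is delivered by only 10% to 25% of providers. The incentive in arm three is paid for documented assistance, and sites are excluded on an assistance criterion. Assistance in this narrower sense is therefore what the trial sets out to change.

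The primary score is broader. If arms differ on it, the difference may lie in advice, assessment, assistance or any mix of these. Rejecting equality of a 5As count does not imply that assistance differs. Because the analysis and power sections give the count the name of one of its parts, a rejection would read as confirming the central hypothesis even if counselling, medication discussion and referral had not changed.

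The natural safeguard would be a listed outcome for assistance itself. The power section shows that the authors wanted such a comparison, but it has no place among the outcomes and no stated data source. Patient use of cessation treatment over the following three months is listed, but that is a different quantity from what the provider delivered at the visit.

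**Working it through.** **1. Setting the sections side by side**

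| Place | What the primary quantity is called or contains |
|---|---|
| Aim one; central hypothesis | Delivery of cessation assistance |
| Abstract | Change in tobacco treatment practices |
| Overview of study design | Delivery of tobacco cessation treatment |
| Primary outcome; Table 3 | Guideline adherence; a count over the 5As |
| MLM approach | Summary score of provider assistance |
| Power section | PEI score, null stated for assistance behaviours |

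The definition covers the 5As, while the label and the null refer to assistance. The assistance rate appears only in the power section.

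**2. Can the other items move more than assistance?** The Performance feedback section gives pilot figures: advice 28% to 49%, then "assess readiness to quit (18% pre, 30% post), and offer assistance (7% pre, 16% post").

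- Advice: 49 − 28 = 21 points.
- Assessment: 30 − 18 = 12 points.
- Assistance: 16 − 7 = 9 points.

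Assume one item per behaviour. The summed gain is then 0.21 + 0.12 + 0.09 = 0.42 index points, with shares of 50%, 29% and 21%. Removing the assistance gain leaves 0.33. So an index of this kind can rise with no change in assistance. The shares are illustrative, for the reasons given under the objection.

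**3. The plan's own PEI power.** Inputs from the power section: effect size (8.40 − 6.24)/2.12 = 1.02, six sites per arm, 100 patients per site, two-sided alpha 0.01, stated power 86%. No ICC is given for this calculation, so 0.22 is borrowed from the GEE paragraph.

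- Design effect: 1 + 99 × 0.22 = 22.78.
- Effective n per arm: 600/22.78 = 26.3.
- Power: Φ(1.02 × √(26.3/2) − 2.576) = Φ(1.13) = 87%.

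This reproduces the stated 86% to within two points. That power belongs to the 5As count and says nothing about assistance alone.

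**4. What the assistance outcome could support.** Same effective n and alpha, post-intervention data only, with

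power = Φ{[Δ√n − 2.576 √(2p̄(1 − p̄))] / √(p₁(1 − p₁) + p₂(1 − p₂))}.

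For 20% against 10%: Δ√n = 0.1 × √26.3 = 0.513; 2.576 × √(2 × 0.15 × 0.85) = 1.301; denominator √(0.09 + 0.16) = 0.5. This gives Φ(−1.575) = 6%.

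| Contrast | Stated power | ICC 0.22 | ICC 0.01 (assumed) | ICC 0 (assumed) |
|---|---|---|---|---|
| 20% v 10% | 82% | 6% | 81% | 99% |
| 30% v 20% | 73% | 4% | 60% | 92% |
| 30% v 10% | 97% | 22% | >99% | >99% |

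The article does not give the correlations needed to model a pre-post gain, so these figures do not show what the fitted model would achieve. They show only that the assistance comparison may be imprecise at the stated ICC.

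**The case against.** The strongest reply is that assistance is not neglected. The power section calls assistance rates a key component of the aims and gives arm-specific rates, a model, an alpha and all three pairwise contrasts. A broad adherence index as primary with assistance analysed separately is a defensible design. The article also sometimes uses the word assistance loosely, for the whole of what the PEI measures. This reply stands in part. The analysis is planned, and what is missing is its place in the outcome lists and its data source. Loose usage does not remove the conflict, because the hypothesis and the incentive use the word for one specific step.

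Three stronger readings are tempting, and the document does not support them.

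- *About four fifths of any index gain would come from outside assistance.* The pilot shares come from chart audit, not exit interviews, and from a single-arm before-after comparison. They also assume one item per behaviour. The split of the eight items is not shown, and two of the three example items are assistance items. In this trial every arm receives training and chart reminders, so part of such a gain would occur in all arms and cancel between them.
- *An effect confined to assistance is diluted by a known factor.* With m assistance items of eight, equal variances and independence, the factor is √(m/8): 0.61, 0.71 and 0.79 for m = 3, 4 and 5. The document fixes neither m nor the correlations, so no single value can be claimed.
- *No conclusion on assistance should be allowed unless the assistance outcome is also significant.* With power that may be as low as shown above, such a gate could block a true conclusion most of the time. Ordering of secondary outcomes is also commonly left to an analysis plan that is not shown.

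**Conclusion.** The point holds as an inconsistency of label, null hypothesis and outcome list. The definition of the score, its name in the analysis section and the null in the power section do not describe the same quantity, and the assistance rate is powered but not listed. The index analysis itself remains valid as a test of guideline adherence. What is not secured is the step from that test to a statement about cessation assistance.

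The size of a possible misreading cannot be derived from the article. The pilot gains of 21, 12 and 9 points show only that items other than assistance can move more. The low power for assistance at an ICC of 0.22 (about 6%, 4% and 22%) rests on a design-effect approximation with post-intervention data alone. The difference from the stated 82%, 73% and 97% is a separate matter. It is used here only as a reason not to make the conclusion conditional on significance.

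**What to change.** 1. Keep the 0-8 index as primary. In the MLM and power sections, call it 5As guideline adherence and state its null as equal adherence scores across conditions.
2. List patient-reported receipt of any assistance as a named secondary outcome in the abstract, the Overview of study design, the Secondary outcomes section and Table 3. Define it from the PEI items that capture it. Counselling and medication discussion are shown in the Primary outcome section. Referral and prescribing appear in the chart-audit definitions but are not shown as PEI items, so the sponsor should confirm whether a referral item exists before the definition is fixed.
3. Analyse it with the logistic GEE already described.
4. Word conclusions so that an effect on the index is reported as guideline adherence. Report the assistance effect with its confidence interval alongside, and use it for any statement about assistance.

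The cost is wording in a few sections and one more reported model. If the PEI items shown are sufficient, no new data are needed; if referral is to be included and is not asked, the definition must be narrower or an item added. The real downside is a more cautious claim about assistance, since its interval may be wide at the stated ICC.

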**Methods/Design:**

Guided by a multi-level, conceptual framework that emphasizes changes in provider beliefs and organizational characteristics as drivers of improvement in tobacco treatment delivery, the current protocol will use a cluster, randomized design and multiple data sources (patient exit interviews, provider surveys, site observations, chart audits, and semi-structured provider interviews) to study the process of implementing clinical practice guidelines for treating tobacco dependence in 18 public dental care clinics in New York City. The specific aims of this comparative-effectiveness research trial are to: compare the effectiveness of three promising strategies for implementation of tobacco use treatment guidelines—staff training and current best practices (CBP), CBP + provider performance feedback (PF), and CBP + PF + provider reimbursement for delivery of tobacco cessation treatment (pay-for-performance, or P4P); examine potential theory-driven mechanisms hypothesized to explain the comparative effectiveness of three strategies for implementation; and identify baseline organizational factors that influence the implementation of evidence-based tobacco use treatment practices in dental clinics. The primary outcome is change in providers’ tobacco treatment practices and the secondary outcomes are cost per quit, use of tobacco cessation treatments, quit attempts, and smoking abstinence.

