#### Eligibility and recruitment of field sites

The selection of clinic sites is guided by our intent to insure that findings will be generalizable to real-world dental healthcare settings serving diverse population of smokers. The trial will be conducted in partnership with 18 public health dental clinics employing at least two full-time dentists, not fully adherent to PHS guidelines, able to accept additional compensation if assigned to the P4P arm and serving low-income patients in the New York metropolitan region. For practical (cost and staffing) reasons, clinic sites will be recruited in six successive waves with three sites enrolled per wave. Site randomization will be conducted using the random permuted block method with stratification by clinic volume (small, medium, large). Prior to enrollment, clinics will be categorized as small (100 to 400 patients per week), medium (401 to 750 patients per week) or large (>750 patients per week) based on the number of adult patients seen per week per the dental director. Clinics whose patient volume is less than 100 patients per week will be excluded. Matching the clusters has several practical and statistical advantages. Of particular importance is that matching offers some control for background effects (*e.g.*, cigarette pricing and other public policy changes) contemporaneous of the current trial [57]. Baseline data collection will be completed prior to randomization. If the baseline providers’ assessment reveals that the site assists more than 60% of patients who smoke, then the clinic will be excluded and replaced with an alternate site of similar patient volume.

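### The primary PEI model most naturally reads as a difference in differences; adjusting for the site's pre-randomization mean is usually more precise and never materially worse

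*Protocol article*

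**What the plan says.** The section on the MLM approach to the primary aim names the outcome: "The primary outcome is the summary score of the PEI assessment of provider assistance (score range 0 – 8". It announces that "A two-level MLM will test of the effectiveness of the implementation strategies", and enters each patient's score "as a function of intervention and time (pre and post intervention", so that the site provides its own comparison from before implementation. The abstract describes the outcome as a change: "The primary outcome is change in providers’ tobacco treatment practices". The limitations paragraph of the Discussion repeats the own-control idea as protection against historical effects.

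Two design facts bear on this. First, baseline precedes allocation. The section on field-site eligibility says "Baseline data collection will be completed prior to randomization", and the General approach, after describing the baseline interviews, continues "Then each site will be randomly assigned and will receive their intervention condition for nine months". Second, the two waves of interviews are with different patients: after the intervention, "another independent sample of 100 smokers will complete patient exit interviews (n = 1,800 post-intervention".

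The article does not write out an intervention-by-time interaction. It does not say whether arm means at baseline are free or held equal, and it does not name the site's baseline mean as a covariate. The covariates it mentions are optional patient characteristics.

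**The concern.** If the arm effect is the difference between arms in pre-to-post change, the estimate subtracts the whole observed baseline difference between arms. Under randomization after baseline that difference is noise: between-site variation that fell unevenly by chance, plus sampling error from a separate set of patients. Subtracting it in full is optimal only when site means barely move between the two waves. Otherwise a partial subtraction, with the weight estimated from the data, is better.

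With six sites per arm, precision rests on site means, so the choice of contrast matters. The 1,800 baseline interviews are already planned. What is at stake is how much precision they add, and whether a change contrast could leave the comparison less precise than the post-intervention interviews alone.

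**Working it through.** **Inputs from the article.** 18 sites, six per arm; 100 interviews per site per wave; effect 1.02 SD; two-sided alpha 0.01; stated power 86%. The ICC of 0.22 is given for the logistic GEE on assistance rates.

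**Assumptions.** The same ICC applies to the PEI. The site autocorrelation (CAC, the correlation of true site levels before and after) is not given, so it is varied from 0 to 1.

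**The plan's own figure.** In SD units, the variance of a site mean is 0.22 + 0.78/100 = 0.2278. The variance of a two-arm difference in post-intervention means is 2 × 0.2278/6 = 0.0759. Normal-approximation power is Φ(1.02/√0.0759 − 2.576) = 87.0%, close to the stated 86% (an ICC of 0.23 gives 85.3%). So 86% reproduces as a post-only two-arm comparison that uses no baseline data.

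**Correlation of observed site means.** r = CAC × 0.22/0.2278 = CAC × 0.966.

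**Variance of an arm difference, relative to post-only:**
- Difference in differences: 2(1 − r). This exceeds 1 when r < 0.5.
- Adjusted for the site baseline mean, slope known: 1 − r².
- Adjusted, slope estimated from 18 sites in three arms: (1 − r²)(1 + 1/13) = (1 − r²) × 14/13.

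The ratio of adjusted to change variance with an estimated slope is (1 + r)/2 × 14/13. It equals 1 at r = 26/14 − 1 = 0.857, that is CAC = 0.857/0.966 = 0.89.

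| CAC | r | Change variance | Adjusted variance (slope estimated) | Ratio | Power, change | Power, adjusted |
|---|---|---|---|---|---|---|
| 0 | 0 | 0.1519 | 0.0818 | 0.54 | 52% | 84% |
| 0.3 | 0.29 | 0.1079 | 0.0749 | 0.69 | 70% | 88% |
| 0.5 | 0.48 | 0.0785 | 0.0627 | 0.80 | 86% | 93% |
| 0.7 | 0.68 | 0.0492 | 0.0444 | 0.90 | 98% | 99% |
| 0.8 | 0.77 | 0.0345 | 0.0330 | 0.95 | >99% | >99% |
| 0.9 | 0.87 | 0.0199 | 0.0200 | 1.01 | >99% | >99% |
| 1.0 | 0.97 | 0.0052 | 0.0055 | 1.06 | >99% | >99% |

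Power is by normal approximation at 1.02 SD; post-only is 87%. A simulation of 40,000 trials gave ratios of 0.801, 0.949, 1.001 and 1.054 at CAC 0.5, 0.8, 0.9 and 1.

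**Small-sample reference distribution.** With t on 15 df (14 after adjustment) all powers fall: post-only 76%; at CAC 0.5, change 74% and adjusted 84%.

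**Sensitivity to the ICC.** At ICC 0.05 the reliability of a site mean is 0.05/0.0595 = 0.840. The reductions at CAC 0.5, 0.7 and 0.8 become about 24%, 14% and 10%. Since r cannot then exceed 0.840, break-even is not reached.

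**The case against.** Four points can be made for the plan.

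1. **The article does not commit to free baseline arm means.** A reader might infer them, but no interaction and no constraint is written. A model with a common baseline mean is also a function of intervention and time, and exact coding is often left to the full protocol or SAP. This stands: difference in differences is the natural reading of the own-control wording and of the abstract's reference to change, but it remains an inference. No patient-level change score is planned, and none is possible with independent samples.

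2. **Adjustment does not always win.** The known-slope formula suggests that it is always at least as precise, with gains of 26%, 16% and 11% at CAC 0.5, 0.7 and 0.8. With 18 sites the slope must be estimated. The gains fall to 20%, 10% and 5%, and the order reverses above CAC 0.89. This stands too. Read literally, a two-level model with one site effect common to both waves implies CAC 1, where change is the slightly better contrast. Values below 1 need a site-by-time effect.

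3. **The change contrast is valid.** A reader might infer bias from the subtraction of chance imbalance. There is none; the cost is precision only.

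4. **The authors have a reason for using each site's baseline**, namely order and historical effects. Adjustment for the site baseline also uses it, and the concurrent arms remain the comparison.

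These points limit the size of the concern but do not remove it, because the trade is lopsided. Adjustment loses at most about 6% of variance, and only where both powers exceed 99%. The change contrast can double the post-only variance.

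**Conclusion.** The point holds as one of efficiency. Read as a difference in differences, the primary contrast is valid but usually less precise than adjustment for the site's baseline mean. It is less precise than ignoring baseline when r is below 0.5. At ICC 0.22 the variance reduction from adjustment is about 20%, 10% and 5% at CAC 0.5, 0.7 and 0.8. Above about 0.89 there is a loss of at most about 6%. The sizes rest on an ICC borrowed from the assistance-rate calculation and on an autocorrelation that the article does not give.

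Adjustment should be described as usually more precise than change and never materially worse, not as always at least as precise. Against post-only it also has a small price when r is near zero: a factor of 14/13, about 8% of variance.

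**What to change.** State the primary contrast explicitly, in one of two forms:

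- Post-intervention PEI score compared between arms in a mixed model with patients nested in sites, adjusted for the site's mean pre-intervention PEI score. The covariate must be the site mean, because the patients differ between waves.
- A model for both waves with arm means constrained to be equal at baseline and with random site and site-by-time effects. The arm effect is then the intervention-by-post term.

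The two are similar but not identical with 18 sites, so one should be named as primary.

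The cost is a sentence of model wording, no new data, and about one site-level degree of freedom (15 to 14), plus any spent on volume-stratum terms if these are added. If site means turn out very stable, a small loss of precision is accepted.
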